### Patient and public involvement statement

Prior to development of the protocol, key stakeholders were informed of the study, including the study sites (ie, selected health centres) and their surrounding communities (ie, catchment areas), the DHO, MoH and the Ministry of Education. We actively sought and incorporated input from these stakeholders into the study objectives and overall design. Community sensitisation will be further strengthened through a community advisory board.

#### Data collection, management and anonymisation procedures

Demographic data and relevant medical history will be collected using password-protected electronic data capturing. Each participant will be assigned a unique participant identification number (PID) at recruitment. This PID will be used in all datasheets and files, and will be linked to the laboratory data, hence, only anonymised data will be used for the analysis. Fully anonymised data will be uploaded daily to a secured on-site server, which is backed up daily to both local and off-site facilities. A logbook containing identifiable information (including name) will be kept separate in a secured location by an authorised member of the study team and will only be accessed by authorised study members. This will allow the study team to recover any missing epidemiological information at a later date (eg, missing vaccination dates) and to facilitate any participants who choose to withdraw consent at any time.

### Statistical analyses

Continuous variables will be summarised by means and SD, or medians and IQRs if the distribution exhibits skew. Categorical variables will be summarised by frequency distributions. Direct effects of the PCV13 schedule change on VT carriage will be ascertained by comparing carriage prevalence in children aged 15–24 months residing in the recruitment clusters of health centres randomised to the 2+1 schedule and those in recruitment clusters of health centres randomised to the 3+0 schedule. Indirect effects will be evidenced by comparing children in the recruitment clusters of health centres randomised to the 3+0 schedule among older children (5–10 years) and HIV +adults. Additionally, data obtained in this study will be compared with those obtained from previous carriage surveys to ascertain any changes in VT carriage prevalence before and after the PVC13 schedule change. Statistical tests will be selected depending on the distribution patterns of the data. Potential confounders and sources of interaction (including age, gender and health centre) will be identified by testing the association between variables and VT carriage and included in the multivariable models when p<0.1. Sensitivity analyses will include assessing impact of (1) receiving only one, only two or all three doses PCV; (2) having document-confirmed PCV vaccination or (3) schedule adherence to within 2 weeks of each scheduled dose on VT prevalence and on the VT distribution.

## Ethics and dissemination

### Ethics approvals

The study has been approved by the Malawi College of Medicine Research Ethics Committee (COMREC; Ref: P05.19.2680), the University College London Research Ethics Committee (Ref: 8603.002) and the University of Liverpool Research Ethics Committee (Ref: 5439).

### Data monitoring external advisory group

The implementation of the study protocol will be reviewed and monitored by an External Advisory Group, providing oversight of the study activities and advise the study team at the time of the interim and final analyses. The group will include experts from the University of Malawi, College of Medicine, the London School of Hygiene & Tropical Medicine and the Medical Research Council.

### Interim analysis and changes to public health policy

On completion of the first carriage survey, an interim analysis will be implemented using data obtained on the VT carriage prevalence among vaccinated children 15–24 months of age. These results will be used to assess possible adaptation of the second community carriage survey. Three possible scenarios are considered: (1) If convincing evidence of major change in carriage prevalence is demonstrated, immediate action will be discussed with the MoH to move to change the schedule and adapt year-3 sampling; (2) If no major change in carriage prevalence is identified, the study will continue as planned; (3) If carriage prevalence has fallen by more than 30% but does not meet the primary threshold of 50%, the second carriage survey will be brought forward by 6 months. Decisions will be reached in consensus between investigators, the Expert Advisory group, and the MoH.

### Informed consent process

The study will only recruit children whose parents/legal guardians have the capacity to provide informed consent or, in the case of adults, are capable of giving consent. Children who are minors but ≥8 years of age will be required to provide informed assent, in addition to parents/legal guardians providing informed consent. Participants will receive both verbal and written information about the study and will be given the opportunity to ask questions and express their doubts and concerns before accepting to take part. They will also be given time to reflect before they come to a decision. An informed consent and/or assent form will be signed and dated by the participant and a member of the research team. The participant will keep a copy of the document, and a second one will be kept in the study file with the Principal Investigator based in Blantyre, Malawi. Participants will be informed of their right to withdraw consent at any point until study ends without the need to provide a reason and without penalty.

## Dissemination policy and plans

Study results will be shared with local stakeholders and published in peer-reviewed journals. Partial results and interim analyses will be shared with the Malawi MoH and other relevant policymakers and decision-making stakeholders. Partial and final findings will be presented at relevant international conferences and meetings. Copies of all published materials and reports will be shared with the research ethics committees and collaborators. We will return to the community partners and work with the community advisory board to report and further disseminate our results into those communities where we worked.

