### Study questions

We will investigate whether a 2+1 PCV13 vaccination schedule (two primary doses at 6 and 14 weeks of age +1 booster dose at 9 months of age), compared with the current 3+0 schedule (three primary doses at 6, 10 and 14 weeks of age with no booster), is superior in reducing VT carriage prevalence among vaccinated children and, consequently, creating a superior herd effect among older children and HIV-infected adults. To assess the effect of a district-wide change from 3+0 to 2+1, this study will address two specific research questions: First, will a 2+1 schedule provide enduring vaccine-induced protection against pneumococcal VT carriage into the second year of life? Second, will the 2+1 vaccine schedule generate stronger herd protection and result in decreased VT carriage in older children and unvaccinated high-risk adults in the general population?

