### A pragmatic study design

This switch to a 2+1 schedule is an initiative led by the MoH and will be implemented within the scope of the routine EPI programme, subject to EPI standard procedures for delivery, monitoring and performance assessment. Implementation of all vaccination activities will be implemented, as per routine practices, by MoH EPI vaccinators through the routine EPI programme. The MoH will monitor completeness of dosing following standard reporting practices within the scope of the EPI. Routine study activities throughout the duration of the 3-year study period will include research nurses providing support and guidance to the EPI vaccination teams through weekly site visits. In addition, research enumerators will monitor patient-retained health passports of a representative sample population of vaccinees to confirm they are receiving the proper vaccine schedule (2+1 or 3+0) assigned to the catchment population of their respective health centre.

The pragmatic design of this study has been assessed through the tool The PRagmatic-Explanatory Continuum Indicator Summary 2 (PRECIS-2).^48^ This tool was developed to help trialists make design decisions consistent with the intended purpose of their trial. To facilitate domain discussion and consensus, PRECIS-2 assesses the pragmatic design through nine domains—eligibility criteria, recruitment, setting, organisation, flexibility (delivery), flexibility (adherence), follow-up, primary outcome and primary analysis—scored from 1 (very explanatory) to 5 (very pragmatic). The report from this tool is in the format of a wheel (figure 2). Results (mean score: 4.4 and range: 3–5) supports that this is largely a pragmatic randomised study undertaken in the ‘real world’ and with usual care and is intended to help support a decision on whether to deliver an intervention.

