### Carriage surveys

The study will include two cross-sectional carriage surveys, implemented 18 and 33 months after the switch to 2+1. Carriage surveys will be conducted using a well-established methodology implemented extensively in the setting,^45 46^ allowing comparability of study results to previous carriage surveys conducted in the area. The sampling frame is illustrated in figure 3.

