### Expected outcomes

The primary endpoint of this study will be the difference in VT pneumococcal carriage prevalence among children aged 15–24 months, comparing those vaccinated with PCV13 in either a 2+1 or 3+0 schedule, 3 years after implementing the switch to a 2+1 schedule. Additionally, the study will evaluate four secondary outcomes: (1) difference in VT carriage prevalence among children 5–10 years old, 18 months and 33 months after 2+1 implementation, (2) VT carriage prevalence among HIV-infected adults aged 18–40 years and receiving ART at the time of sampling, (3) VT carriage prevalence among infants aged 9 months, who will have received three primary doses (3+0 health centres) or two primary doses (2+1 health centres) prior to the booster dose, 9 months after the implementation of the 2+1 schedule and (4) prevalence of multiple serotype carriage, 18 and 33 months after 2+1 implementation

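### The dissemination plan lets arm-level 18-month results in the primary age group circulate beyond the interim decision-makers, with no hold until the second survey supplies the primary endpoint

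*Protocol article*

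**What the plan says.** The section on dissemination policy and plans makes two commitments about results that are not final. The first is to policymakers: "Partial results and interim analyses will be shared with the Malawi MoH and other relevant policymakers and decision-making stakeholders". The second is to the scientific public: "Partial and final findings will be presented at relevant international conferences and meetings". Neither is tied to completion of the second survey, and neither separates arm-level results from pooled ones.

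On timing, the carriage surveys section states: "The study will include two cross-sectional carriage surveys, implemented 18 and 33 months after the switch to 2+1". The expected outcomes section defines the endpoint: "The primary endpoint of this study will be the difference in VT pneumococcal carriage prevalence among children aged 15–24 months", placed "3 years after implementing the switch to a 2+1 schedule". The second survey is therefore the one that supplies the primary result.

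The interim section analyses the same age group after the first survey and gives three scenarios:
- Scenario 1, convincing evidence of a major change: a schedule change is discussed with the MoH and year-3 sampling is adapted.
- Scenario 2: "If no major change in carriage prevalence is identified, the study will continue as planned".
- Scenario 3, a fall of more than 30% that misses the 50% threshold: the second survey comes 6 months earlier.

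The investigators, the advisory group and the MoH decide together.

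On delivery, the pragmatic design section states: "Implementation of all vaccination activities will be implemented, as per routine practices, by MoH EPI vaccinators through the routine EPI programme".

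**The concern.** The first survey yields a comparison of 2+1 with 3+0 in the primary age group while the primary cohort is still being vaccinated. The 2+1 schedule is "two primary doses at 6 and 14 weeks of age +1 booster dose at 9 months of age", so the 9-month visit is one of the points at which the arms part. If a result favouring 2+1 became widely known before that visit, staff at a 3+0 centre or caregivers in its catchment could act on it. A 3+0 child might get an additional dose, or be taken to a neighbouring 2+1 centre.

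Such children could stay in the control group, because the statistical analyses section compares children by the cluster they live in. The month-33 difference would shrink towards zero for a reason unrelated to the schedules. The article already lists contamination between clusters as a limitation, but only through where children live or move. Wider release of interim results would add a second route, and one the investigators control.

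**Working it through.** **1. The plan's own sample size.** Inputs from the sample size section and Table 1: 14% v 7%, 80% power, alpha 0.05 (taken as two-sided), ICC 0.005, 40 children per cluster, 10 clusters per arm.
- A two-proportion calculation with pooled variance and no continuity correction gives 300 per arm.
- Design effect = 1 + (40 − 1) × 0.005 = 1.195.
- 300 × 1.195 = 358.5, against 358 in Table 1. The figure reproduces.
- At the planned 400 per arm, the effective size is 400 / 1.195 = 334.7 and power is 84%.

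**2. When the primary cohort reaches the 9-month visit.** Birth month = survey month − age (24 to 15 months). Visit month = birth month + 9.

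| Second survey | Births, months | 9-month visits, months |
|---|---|---|
| Month 33 (planned) | 9–18 | 18–27 |
| Month 27 (scenario 3) | 3–12 | 12–21 |
| Month 36 (if 3 years is read literally) | 12–21 | 21–30 |

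**3. Share of visits after release at month T.** The documents give no release date. I assume 3 or 6 months for fieldwork, serotyping and analysis, so T = 21 or 24.
- Survey at month 33: share = (27 − T) / 9, which is 67% at T = 21 and 33% at T = 24.
- Survey at month 27: the last visits are at month 21, so the share is 0% at either date.

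**4. Illustrative dilution, survey at month 33.** Assume a fraction u of the 3+0 children still to be seen takes an extra dose, and that their carriage falls to 7%. Then 3+0 prevalence = 0.14 − 0.07 × share × u. The documents give no value for u.

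| T | u | 3+0 prevalence | Difference, points | Power |
|---|---|---|---|---|
| – | 0 | 14.0% | 7.0 | 84% |
| 21 | 10% | 13.5% | 6.5 | 80% |
| 21 | 20% | 13.1% | 6.1 | 74% |
| 21 | 40% | 12.1% | 5.1 | 62% |
| 24 | 10% | 13.8% | 6.8 | 82% |
| 24 | 20% | 13.5% | 6.5 | 80% |
| 24 | 40% | 13.1% | 6.1 | 74% |

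**5. Which scenario carries the exposure.** Suppose the true rates at the interim are 14% v 7%, with 400 per arm and design effect 1.195. The interim section gives no number for convincing evidence, so I read scenario 1 as an observed reduction of at least 50% and scenario 2 as one under 30%.
- Scenario 1: about half of trials (50% by normal approximation, 52% by simulation).
- Scenario 2: about 7–8%.
- Scenario 3: the remainder, about 40%.

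A persuasive interim is therefore likely under the design assumptions. Where it falls in scenario 3, step 3 shows almost no exposure. Where it falls in scenario 1, the text promises a discussion of change, not an end to the comparison, so the month-33 survey may still run with most 9-month visits to come.

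**The case against.** The strongest reply is that the interim rule already pairs each result with a calendar, and that most pairings are harmless. Under scenario 3 the survey moves and the visits are over by month 21. Under scenario 2 the date stands, but an unimpressive result gives nobody much reason to depart from 3+0. Both points are right and narrow the concern to scenario 1 with the comparison still running.

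Safeguards also exist. Research nurses visit weekly, enumerators check health passports against the assigned schedule, sampling favours households near the centre, and children must have passport evidence of a full schedule. These would detect some departures. They do not remove the motive, and the passport checks cover only a sample. The inclusion criteria do not say outright how a 3+0 child with an extra dose is handled. If such children were excluded, the dilution in step 4 would be smaller.

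It is also fair that this is a ministry-led, policy-facing study. The MoH must see the interim result to take part in the decision, so no rule can close that route. The avoidable part is release to other policymakers and to conferences, and the documents trace no path from those audiences to vaccinators in Blantyre.

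A reader might infer that the plan schedules a conference presentation of the arm comparison before the primary survey. It does not. No date is given, and the unfinished findings could come from the 9-month survey, the schoolchildren or the adults. The text permits early arm-level release without requiring it. Detailed confidentiality terms may also sit in the full protocol, but the article's wording on release is affirmative and unqualified.

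**Conclusion.** The point stands in a limited form. As written, the dissemination section allows the 18-month comparison of 2+1 with 3+0 in children aged 15–24 months to travel beyond those who need it for the interim decision, before the primary endpoint is measured. With the survey at month 33, the cohort's 9-month visits fall in months 18–27, so early release could affect how the control arm is vaccinated. The exposure matters mainly under scenario 1 when the schedule is not changed at once. It is small under scenario 2 and close to nil under scenario 3.

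A reader might take the power table as a forecast. It is not one. Release date and uptake are both assumed, full 2+1-like protection is credited to every extra dose, and nothing in the documents says contamination by this route will occur. The table shows only that the margin over 80% power is about 4 points, so modest contamination would use it up. The case for change rests on the low cost of protecting the primary comparison, not on a predicted loss.

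**What to change.** Amend the dissemination section. While the comparison continues, the 2+1 versus 3+0 results in children aged 15–24 months from the 18-month survey are shared in confidence only with the investigators, the External Advisory Group and the MoH decision-makers, together with the policy advisers they need for the interim decision. These results are not presented at conferences, to communities, or to EPI and survey field staff until second-survey swabbing and serotyping are complete. Results pooled across arms may be presented at any time. If the interim decision ends the comparison, the restriction lapses.

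The cost is one paragraph of wording and a delay in public presentation of that one comparison of up to about 33 − 18 = 15 months. Policy action through the interim meeting is unaffected.
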